#### Blinding

The biostatistician will randomize deidentified fitness class sites into arms and will keep this blinded from the principal investigator (PI: [name]) and project coordinators while recruitment occurs. All the study team members will be blinded except for the senior ethnographer, field ethnographer, community champions, and community partners.

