### Patient and Public Involvement

The intervention was developed in this New York City–based study through a co-design process with women from Washington Heights, New York City [3,10]. We established collaborations with 3 community partner organizations (Shape Up NYC, Jovie, and the West Side Campaign Against Hunger [WSCAH]). These partners participate in research team meetings and in the study design. Partner details are provided as follows:

Shape Up NYC: New York City Department of Parks and Recreation programs include Shape Up NYC, a free group fitness program offering 87 fitness classes at 60 locations across the 5 New York City boroughs. Shape Up NYC will determine and schedule available study sites and classes in coordination with the intervention.Jovie: Jovie is a professional childcare company that provides care for families and businesses. We partnered with Jovie during the feasibility study, and they will continue providing childcare.WSCAH: WSCAH is one of the largest food pantries that serves New York City and is distinctly committed to providing healthy food through a customer-choice supermarket-style pantry. WSCAH will coordinate volunteer activities and food delivery for participants in the arm receiving peer support.

These partners are members of our community advisory board (CAB). The CAB also includes 4 community liaisons and 2 community champions. The community liaisons are individuals who represent or serve our target communities, the community partners represent our organizational partners, and the community champions are local women who will help facilitate peer support activities.

The main CAB functions are to ensure that the study’s research strategies and design respect and serve our participants and make sense “in the real world.” The CAB will meet quarterly to troubleshoot any problems with the trial procedures. They will also bring community concerns or ideas to the research team.

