### Participants

#### Eligibility Criteria

The trial will enroll mothers aged 18 years and older, who understand or speak English or Spanish, have children younger than 12 years of age (because younger children require more care, and we are focused on preventing chronic disease among premenopausal women), own a mobile phone, and live in nearby zip codes surrounding Shape Up NYC sites. Mothers must also meet income requirements, with total household income less than or equal to 165% of the area median income (calculated by household size).

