#### Clusters

We will recruit 720 participants into 24 Shape Up NYC classes, across 1 pilot wave (n=90) and 7 study waves (n=630) over 2 years (Figure 2). Shape Up NYC class sites that allow research and have adjacent space for childcare will be eligible for selection. We will randomize each wave of 3 sites into 1 of 3 arms, using computer-generated random numbers, and run the program for 12 weeks. We will first randomize the class sites and then recruit participants into them while blinded.

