### Recruitment

We will use multiple recruitment methods to identify and recruit participants. We will distribute paper and digital flyers and advertise FT4W on social media platforms including Facebook and Instagram. WSCAH, Jovie, and their partner community-based organizations will circulate our recruitment flyer to their constituents via email. Our project coordinator will do direct in-person outreach at community events and schools. The project coordinators will follow up with individuals interested in participating in the study by phone, email, or SMS text message.

To mask the purpose of the study, we will tell potential participants that the study seeks “to find the best way to connect moms living in the same neighborhood.” Eligible participants will provide informed consent after reviewing the institutional review board–approved document that explains the study and their involvement in it by providing their digital signature.

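### Recruitment after site randomisation is called blinded, but two partners exempt from blinding circulate the recruitment flyer, so concealment is not secured for everyone who takes part in recruitment

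*Protocol article*

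**What the plan says.** The Clusters section fixes the order of events: "We will first randomize the class sites and then recruit participants into them while blinded". Table 2 likewise places its allocation column before enrolment.

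The Blinding section protects the people who run enrolment: "The biostatistician will randomize deidentified fitness class sites into arms and will keep this blinded from the principal investigator", and from the project coordinators, for as long as recruitment lasts. The next sentence lists the exceptions: "All the study team members will be blinded except for the senior ethnographer, field ethnographer, community champions, and community partners".

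Patient and Public Involvement names three community partners: the city fitness programme, the childcare company and the food pantry. The Recruitment section gives two of them a task: "WSCAH, Jovie, and their partner community-based organizations will circulate our recruitment flyer to their constituents via email". It gives the later contact to blinded staff: "The project coordinators will follow up with individuals interested in participating in the study by phone, email, or SMS text message". Potential participants are told a masked study purpose.

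Under Quantitative Analysis, the primary model is adjusted only for baseline covariates that turn out to differ between arms.

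**The concern.** In a cluster trial that enrols after allocation, randomising the sites does not by itself make the participants comparable. Comparability also requires that those who influence who hears of the study, and who comes forward, do not know which arm each site is in. Here the two partners that send the flyer also deliver components specific to certain arms: childcare in arms B and C, and volunteering and food delivery in arm C. Their constituents may plausibly differ in need for childcare or interest in group activity, which are the factors the intervention works through.

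If knowledge of the arm affected whom a partner mailed, or where, the arms could differ at entry in motivation or need. An intention-to-treat analysis keeps women in the arm to which their site was allocated, so it would carry such a difference into the comparison. The comparisons at stake are B versus A (aim 1), and C versus B and C versus A (aim 2).

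**Working it through.** The article gives no figure to reproduce on this point. The check sets its statements side by side.

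1. **Order.** Sites are allocated, then women are recruited (Clusters; Table 2). Concealment during recruitment therefore matters.
2. **Who is kept unaware, and when.** The principal investigator and project coordinators, during recruitment (Blinding). The time limit is attached to them only.
3. **Who is exempt, and when.** Both ethnographers, the champions and the community partners (Blinding). No start time is given for their knowledge of the allocation.
4. **Who has a recruitment task.** The coordinators, plus the childcare provider, the food pantry and those two organisations' own partner bodies (Recruitment).
5. **Overlap of 3 and 4.** The childcare provider and the food pantry: two of the three named partners. The ethnographers and champions have no task in the Recruitment section.
6. **What allocation would tell those two.** Each wave has three sites, one per arm. Knowing which sites need childcare identifies the arm A site. Knowing which site needs pantry activities identifies the arm C site.
7. **Whether outreach can bear on an arm.** Women must "live in nearby zip codes surrounding Shape Up NYC sites". Each site is one cluster in one arm, so outreach weighted towards one locality would feed one arm more than another. The article does not say whether the partner mailing is the same for all sites.
8. **What limits the route.** The flyer is the study's own. No section has partners screening, taking consent or assigning women to sites. Coordinators follow up interested women. The purpose is masked. Partner email is one channel among several, alongside paper and digital flyers, social media and in-person outreach.
9. **What the analysis would catch.** MVPA is measured by accelerometer at baseline (Baseline Assessment), so a baseline MVPA gap would be visible. Adjustment depends on the gap being judged an imbalance, and it cannot reach unmeasured motivation.

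**Size.** Bias in a between-arm comparison would be roughly the difference between arms in the share of women recruited selectively, multiplied by the difference in mean MVPA between those women and the rest. The article gives neither quantity, so no value follows.

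**Scope for change.** The planned total is 720 (Clusters) and 471 were enrolled at manuscript submission (Results). If all 471 count towards the 720, then 720 − 471 = 249 places remained, and 249/720 = 35%. Fewer may remain now.

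**The case against.** The strongest reply is that the two sections can be reconciled. The first sentence of Blinding identifies whose ignorance protects recruitment, namely the people who contact and enrol women, and the Clusters statement fits that. The exempt roles mostly deliver or observe the intervention, and partners may learn the allocation only once a wave is full. This is also a condensed article, and distribution details often sit in a fuller document.

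Much of this stands. It rules out several stronger readings that a reader might be tempted to make:

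- *That the plan flatly contradicts itself.* It does not. What is missing is a time point. The benign timing is possible but not stated.
- *That partners act as recruiters who steer women to sites.* The article describes only the forwarding of a flyer. Nothing says the mailing is selective or site-specific, and the zip-code rule also limits what a mass email could do.
- *That allocation leaks to blinded staff in meetings.* Of the partners the article says "These partners participate in research team meetings and in the study design". It does not say that allocation is discussed there.
- *That the bias can be sized.* One could set an assumed gap in SD units against the detectable effect of 0.68, but no such gap has a source in the article.
- *That the analysis ignores baseline differences.* It plans adjustment for covariates found to be unbalanced.

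The reply does not remove the point. Silence on distribution details would be no finding in an article. This article, however, calls recruitment blinded, exempts the partners without limit of time, and has two of them mail the flyer. Follow-up by blinded coordinators and masking of the purpose do not control who receives the flyer in the first place.

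**Conclusion.** The point holds in limited form. Blinded recruitment is secured for the principal investigator and coordinators, but not for the two partners that circulate the flyer. That leaves a route to differential recruitment. The article does not show that the route has been used, and the size and direction of any bias cannot be derived from it.

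The conclusion assumes that the exemption applies as written, with no time limit. If partners in fact learn each wave's allocation only after its enrolment closes, one added sentence settles the recruitment part. The correction is worth making because it is cheap and a selection difference cannot be fully repaired in analysis. It is not a reason to distrust the trial as a whole.

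**What to change.** **Remaining waves.** State when partners and champions learn the allocation, and withhold it until that wave's enrolment closes. Before then, give only arm-neutral notice of dates and staffing. This is feasible because every eligible site must already have adjacent space for childcare, and by design two of the three sites in a wave need it. At up to 45 children per site (Sample Size), the provider can be told to plan for up to 2 × 45 = 90 places without being told which sites. Champions have no stated recruitment task; including them is a precaution. Ethnographers have none either and need not be included.

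**If partners need earlier notice.** Limit their outreach to one identical mailing covering all three sites of the wave, with site assignment made by the blinded coordinators.

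**All waves, including those completed.** Pre-specify baseline MVPA as a covariate in the primary model, whether or not it looks unbalanced. Report baseline characteristics by arm, and recruitment source by arm where it was recorded.

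**Cost.** Partners get shorter notice to finalise staffing; the article gives no lead time, so this should be agreed with them. No extra participants or measurements are needed. The article expects 75% accelerometer adherence, so some women will lack a valid baseline reading. The handling of a missing baseline value should be stated with the covariate, for example within the multiple imputation that is already one of the planned options for outcomes.

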#### Sample Size

We powered the study to compare the main intervention effects on the primary outcome, which is the average time spent in moderate to vigorous physical activity (MVPA) per week. We plan to enroll 7 sites per study arm (excluding the pilot wave), with about 30 participants with up to 45 children per site. We assume an attrition rate of 30% based on our feasibility study as well as another similar study [19] and an additional 25% accelerometer nonadherence rate based on previous studies [19,20], yielding an average 15 participants per site. Previous studies show that the intraclass correlation coefficient is ~0.15, and we expect a coefficient of variation of 0.5 in the number of participants across different sites. For aim 1, with 80% power, the minimum detectable effect size for the comparison of intervention arm B versus control arm A on average time spent in MVPA is Cohen *d*=0.68 at 5% significance. For aim 2, we will use the Bonferroni correction to adjust for multiple comparisons of arm C versus arm B and arm C versus arm A. With 80% power, the minimum detectable effect size for each comparison is Cohen *d*=0.75 at 5% significance. A previous physical activity intervention study with mothers led to an 80-minute increase in average time spent in MVPA [20]. Specifically, at posttest, the experimental group performed a mean of 154.8 (SD 45.3) minutes of physical activity, whereas the control group reported a mean of 74.6 (SD 44.4) minutes. This yields an effect size of *d*=1.8; thus, we are adequately powered for aims 1 and 2. Finally, quantitative analyses are not fully appropriate to examine intersectionality (eg, too reductionist), rendering a power analysis inappropriate; instead, we will integrate the statistical analysis with qualitative data to evaluate aim 3.

### Recruitment

We will use multiple recruitment methods to identify and recruit participants. We will distribute paper and digital flyers and advertise FT4W on social media platforms including Facebook and Instagram. WSCAH, Jovie, and their partner community-based organizations will circulate our recruitment flyer to their constituents via email. Our project coordinator will do direct in-person outreach at community events and schools. The project coordinators will follow up with individuals interested in participating in the study by phone, email, or SMS text message.

To mask the purpose of the study, we will tell potential participants that the study seeks “to find the best way to connect moms living in the same neighborhood.” Eligible participants will provide informed consent after reviewing the institutional review board–approved document that explains the study and their involvement in it by providing their digital signature.

### Interventions

#### Fitness Classes (All Arms)

Shape Up NYC offers classes that occur weekly for 1 hour free of charge to consenting participants in all 3 arms. Trained Shape Up NYC staff or volunteers lead the fitness classes, which include activities such as yoga, Zumba, and dance fitness. We will invite participants to attend the same scheduled class each week for the duration of their involvement in the 12-week study.

#### Childcare (Arms B and C)

Arms B and C will receive childcare from Jovie in an adjacent space to the fitness class.

#### Peer Support Activities (Arm C Only)

##### Overview

In addition to the fitness class and childcare, arm C will also receive peer support activities. Peer support activities will consist of group smartphone messaging facilitated by community champions, volunteer activities at food pantries, free deliveries of food pantry groceries, and group play dates at local playgrounds.

We structured group activities within the context of intergroup contact theory [21], social penetration theory [22], updated meta-analyses of this work [23,24], and research team members’ prior experience [25-27]. In short, positive communication and disclosure are essential to relationship building, which builds social cohesion. Sharing personal information (disclosure) and spending time together yield the largest effects in meta-analyses—these forms of intimacy grow over the course of developing relationships [22], and growth is more likely when anxiety is reduced and comfort is increased [28]. Anxiety reduction is the most important factor during the initial stages of developing social cohesion, hence our strategic structuring of peer support activities. Our intervention includes a task-based interaction (volunteer activities) where cognitive demand is low and interactional roles are clear. The focus is on the task, rather than developing relationships, reducing the pressure of interaction. As the volunteer activities continue, they also offer the opportunity for group members to enhance empathy, another salient component of cross-group relational development. Mediated interaction (group messaging) supports new relational development through a disinhibiting effect, lowering inhibitions and increasing comfort and disclosure [29].

##### Community Champions

Two bilingual (Spanish or English) community champions will foster social support and participation among arm C participants.

##### Weekly Playdates

Participants in arm C will be offered weekly group playdates for a total of 12 during the intervention. We will invite participants to bring their children to playgrounds in Shape Up NYC neighborhoods, where mothers can collectively watch their children play but also chat and reinforce social bonds. The first 2 playdates will have community champion–facilitated activities to help mothers get to know each other and to reduce the social effort and anxiety often associated with meeting new people.

##### Food Pantry Volunteering

We will invite arm C participants to volunteer as a group to help package food boxes during monthly events with WSCAH at one of their main locations. There is no childcare available for this activity, so participants will be told that they should not bring their children. Most volunteering opportunities are during the day (around 10 AM) on weekdays, and shifts are a maximum of 2-3 hours.

##### Free Grocery Delivery

In the first week of the intervention, arm C participants will also be provided with a link to WSCAH’s enrollment to opt into the home delivery of free groceries once per month for the 12-week intervention. There are no eligibility criteria to receive food from WSCAH, and participants will be eligible even if they do not volunteer.

#### Text Messages (All Arms)

##### Arms A and B

Arms A and B will receive individual text messages with a reminder for their weekly fitness class only.

##### Arm C

Arm C will be assigned to a messaging group with other mothers through WhatsApp, where community champions will “nudge” peer support and participation in activities through group messages. Community champions will follow scripted messages that remind participants when their next fitness class or peer support activity takes place. In addition, they will send weekly (prescripted) conversation prompts to “nudge” social interaction and will be able to “go off script” in response to organic group interactions. Participants will be allocated to groups first by language preference (ie, some groups may be in Spanish and some in English). The goals of the text messaging groups are (1) to encourage relationship-building, (2) to encourage participation in activities, and (3) to provide social support of various types (emotional, informational, etc).

### Outcomes

#### Primary Outcome: Physical Activity

The primary outcome will be total minutes of time spent in MVPA per week. We will objectively assess weekly MVPA, total physical activity, sedentary time, and sleep using a blinded research-grade wrist-worn accelerometer (Axivity AX3) in all groups.

#### Secondary Outcomes

##### Self-Reported Physical Activity

To overcome missing accelerometer data, we will gather self-reported physical activity data using the validated International Physical Activity Questionnaire (IPAQ) [30]. IPAQ asks participants to report the types and frequency of physical activities they have participated in over the past 7 days. IPAQ is reported as a score used to categorize people as having high, moderate, or low levels of physical activity.

##### Health Status and Well-Being

We will measure health status and well-being using 2 standardized surveys: EuroQol 5 Dimension 5 Level [31] and ICEpop Capability Measure for Adults [32]. EuroQol 5 Dimension 5 Level is a generic measure of health status that includes 5 dimensions: mobility, self-care, usual activities, pain, and anxiety or depression. ICEpop Capability Measure for Adults will capture the broader concept of well-being via 5 dimensions: feeling settled and secure; love, friendship, and support; being independent; achievement and progress; and enjoyment and pleasure.

##### Implementation Outcomes

###### Maintenance and Sustainability

Recent advancements in implementation science distinguish maintenance from sustainability by defining the amount of time, with maintenance lasting 6 months or more and sustainability beginning at 1 year or more. We will assess maintenance and sustainability at the organizational level through interviews with 6 stakeholders, 3 from Shape UP NYC and 1 each from Jovie, WSCAH, and the study team. We will use the Extension of the Reach, Effectiveness, Adoption, Implementation, and Maintenance framework to guide our questions.

###### Fidelity

The fidelity of the intervention will be measured during the 12-week trial periods in each wave. We will measure the dose delivered in each cluster by tracking the number of fitness classes and peer support activities offered, childcare availability, and the number and type of texts sent in each group. We will also measure the dose received according to attendance to all components of the intervention (fitness class, childcare, play dates, and volunteer activities) and the type and number of text message engagements. The field ethnographer will also observe how the fitness instructor delivers the class (physical activity level) and the interactions among participants before, during, and after the class (social cohesion).

###### Attendance

An additional process outcome will be attendance at fitness classes. Participation rates are arguably the most important process outcome of interest when evaluating the success of an intervention like FT4W. Shape Up NYC takes attendance at each fitness class, and community champions will take attendance for the peer support activities to understand participation, retention, and attrition levels.

